### Randomization

After confirming eligibility, patients are registered using an independent central registration system. They are randomized in a 1:1 ratio to receive either diclofenac sodium 0.1% cream or a placebo cream using the minimization method, adjusted for sex (male vs. female), planned dose of capecitabine (≥ 800 mg/m^2^, < 1000 mg/m^2^, ≥ 1000, < 1250 mg/m^2^, ≥ 1250 mg/m^2^), and participating institution.

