### Endpoints

The primary endpoint is the incidence of grade ≥ 2 HFS within 3 months. Secondary endpoints include time to onset of grade ≥ 2 HFS, time to onset of grade ≥ 1 HFS within 3 months, incidences of dose reduction, schedule delay, discontinuation due to capecitabine-induced HFS, an incidence of grade ≥ 2 peripheral sensory neuropathy (subgroup analysis will be performed in patients treated with oxaliplatin), and incidences of any grade capecitabine-related adverse events (nausea, vomiting, appetite loss, diarrhea, oral mucositis, pigmentation, abnormality of liver and renal functions, and neutropenia).

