### Sample size calculation

Based on previous RCTs evaluating the preventive effect for HFS, the incidence of grade ≥ 2 HFS within 3 months in the control group without preventive measures was approximately 40% [19, 20, 36]. Accordingly, the incidence of grade ≥ 2 HFS in the placebo arm is assumed to be 40%. It is expected that diclofenac sodium 0.1% cream will suppress grade ≥ 2 HFS within 3 months by 15%, resulting in an anticipated incidence rate of 25%. With a power of 80% and one-sided α of 5%, the required sample size is 160 patients in each arm. Therefore, the target number of enrolled patients is 320. No interim analysis is planned. Sample size calculations will be performed using SAS Studio 3.8.

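### The 160 patients per arm called required do not follow from the printed inputs, which give about 120 per arm; no loss allowance or other reason for the difference is stated

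*Protocol article*

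**What the plan says.** Under Endpoints, the primary endpoint is binary: "The primary endpoint is the incidence of grade ≥ 2 HFS within 3 months". Under Randomization, allocation is 1:1 between two creams. Under Sample size calculation, "the incidence of grade ≥ 2 HFS in the placebo arm is assumed to be 40" per cent, and diclofenac is expected to lower the incidence "within 3 months by 15%, resulting in an anticipated incidence rate of 25" per cent. The error rates and the result come in one sentence: "With a power of 80% and one-sided α of 5%, the required sample size is 160 patients in each arm". The next sentence doubles this to the enrolment target: "Therefore, the target number of enrolled patients is 320".

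The section plans no interim analysis, so no adjustment for repeated testing enters the number. It states no allowance for loss or non-evaluable patients and does not name the test behind the calculation.

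**The concern.** All the inputs of a two-proportion calculation are printed, so the result can be checked, and it does not come out at 160. The number is presented as what the stated alpha and power demand, and it passes straight into the enrolment target with no step for loss between the two.

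What is at stake is less the size of the trial than the meaning of the figures around it. A reader cannot tell whether 160 is an evaluable number or an enrolled number, whether the design power is 80% or nearer 90%, or whether the calculation was run at the printed alpha. The last of these touches the decision threshold of the primary test. With 64 placebo events out of 160, for example, an uncorrected test needs a difference of 15 events (9.4 points) at one-sided 5% and 17 events (10.6 points) at one-sided 2.5%. A difference of 15 or 16 events would be positive at the first level and negative at the second.

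**Working it through.** **Inputs (protocol article).** Placebo rate p1 = 0.40, diclofenac rate p2 = 0.25, difference d = 0.15, one-sided alpha 5%, power 80% (all from Sample size calculation); 1:1 allocation (Randomization); binary endpoint (Endpoints).

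**Formula, per arm, pooled variance under the null:**

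n = [z(1−α)·√(2·p̄·(1−p̄)) + z(power)·√(p1(1−p1) + p2(1−p2))]² / d²

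with p̄ = (0.40 + 0.25)/2 = 0.325, √(2 × 0.325 × 0.675) = √0.43875 = 0.6624, and √(0.24 + 0.1875) = √0.4275 = 0.6538.

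**Attempt to reproduce 160 from the printed error rates.**

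n = (1.645 × 0.6624 + 0.842 × 0.6538)² / 0.0225 = (1.0895 + 0.5503)² / 0.0225 = 119.5, so 120 per arm.

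Other usual methods with the same inputs:

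| Method | n per arm |
|---|---|
| Pooled variance | 120 |
| Unpooled variance | 118 |
| Arcsine | 120 |
| Continuity-corrected | 132.5, so 133 |
| Fisher's exact test, power computed exactly | about 132 (power 80.1%) |

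The printed 160 is 33% above 120 (160/120 = 1.33) and about 20% above 133 (160/133 = 1.20). Rounding or choice of test does not bridge that.

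**Power at 160 evaluable per arm.**

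z(power) = (d·√n − z(1−α) × 0.6624) / 0.6538

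- One-sided 5%: (0.15 × 12.649 − 1.0895)/0.6538 = (1.8974 − 1.0895)/0.6538 = 1.236, so 89.2%. Fisher: 87.1%.
- One-sided 2.5%: (1.8974 − 1.2982)/0.6538 = 0.916, so 82.0%. Fisher (two-sided 5%): 79.0%.

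**Routes that lead to about 160.**

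| Route | Arithmetic | Stated in the article? |
|---|---|---|
| Printed alpha and power, pooled formula, 25% loss | 120/0.75 = 160 | Loss not stated |
| Printed alpha and power, continuity correction or Fisher, about 17% loss | 133/160 = 0.83, so 1 − 0.83 = 0.17 | Loss and test not stated |
| One-sided 2.5% (two-sided 5%), 80% power, 5% loss | 152/0.95 = 160 | Alpha differs, loss not stated |
| One-sided 5%, about 90% power, no loss | 166 for 90%; 160 gives 89.2% | Power differs |

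These routes differ in alpha, in power or in the evaluable number, and nothing in the article selects among them.

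**Sensitivity of the 2.5% route to loss.** At one-sided 2.5% with the pooled formula, 10% loss leaves 144 per arm: (0.15 × 12 − 1.2982)/0.6538 = 0.767, so about 78% power.

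**The case against.** The strongest defence is that this is a condensed article. The full protocol may hold a loss allowance and name the test, and an article commonly leaves such details to it. The text makes some loss plausible: study treatment stops whenever capecitabine stops (Discontinuation of interventions), and the Discussion cites a median progression-free survival of about 3.2 months for capecitabine monotherapy in advanced breast cancer against a 3-month endpoint. With an allowance of 17% to 25%, the printed alpha, the printed power and 160 enrolled per arm all stand, and only the description of 160 as the required number is loose.

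This part stands: a reader might infer that the printed figures cannot all be true, and that goes too far. It does not remove the point. The missing allowance is not the complaint; the complaint is that the article ties 160 directly to the printed alpha and power and then doubles it. The Discussion also expects most participants to continue capecitabine for 3 months and gives no figure for loss.

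A second objection is that the surplus is harmless, since power at the printed alpha exceeds 80%. That is right as far as power goes: with the pooled formula, even 25% loss leaves 120 per arm and 80% power at one-sided 5%. What remains open is which calculation lies behind the number.

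A reader might also infer, because 152/0.95 is exactly 160, that the trial was really designed at one-sided 2.5%. The article prints one-sided 5% and no other alpha, and other unstated routes reach the same number. The match is a back-calculation and not evidence of the intended threshold.

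**Conclusion.** The point holds: the stated sample size does not follow from the stated inputs. They give about 120 per arm (132 to 133 on the more conservative methods) against 160 printed, and 160 evaluable per arm gives about 89% power (87% with Fisher) against 80% printed. This rests on the article's own 40% and 25%, equal allocation, one comparison of two proportions and no loss.

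The document does not show which element is wrong or missing. It does not support saying that the trial is under-powered on its printed assumptions, that its type I error at the printed level is compromised, or that alpha must be 2.5%. One-sided 5% is a design choice and not an arithmetic error. Because the alpha and power of the primary analysis in a phase 3 trial are involved, the paragraph should be corrected before unblinding.

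**What to change.** Keep 320 patients and rewrite the paragraph so that its figures agree, according to how 160 was actually obtained:

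- If one-sided 5% and 80% power are right, either state that about 120 evaluable per arm (132 to 133 with Fisher or a continuity correction) gives 80% power and that 160 gives about 89% with no loss, or state the loss allowance that takes the required number to 160.
- If the calculation was done at one-sided 2.5% (two-sided 5%) or for about 90% power, correct the printed alpha or power before unblinding.

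In either case make the protocol, SAP and registry entry match. The cost is one paragraph and the matching entries, with no extra patients.

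Moving to one-sided 2.5% as a new choice is optional and has a price: with 160 per arm, power is 82% (79% with Fisher) if nobody is lost and about 78% with 10% loss.

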### Management of severe HFS occurrence

In the event of a severe HFS, the study drug application will be discontinued immediately, and treatment with highly potent topical steroid-based therapy should be prioritized in both groups. The principal investigator and research assistants will administer appropriate treatment to the study participants, take the best possible measures, and document the adverse event in the medical record or case report form. Observation of the study participants after adverse events, including illnesses, will be followed up until the event disappears or until the principal investigator or research assistant determines that follow-up is no longer necessary.

## Discussion

This study investigates the preventive effect of topical diclofenac sodium 0.1% cream for capecitabine-induced HFS.

According to the Common Terminology Criteria for Adverse Events version 5.0, grade 2 HFS is defined as a painful skin change, including delamination, blistering, and bleeding, which significantly reduces patients’ QOL. It often leads to treatment interruption, dose reduction, or even discontinuation of capecitabine. Preventing grade ≥ 2 HFS is expected not only improve patients’ QOL but also maintain treatment intensity. As reducing the overall incidence of HFS is more clinically meaningful than merely delaying its onset, the incidence of grade ≥ 2 HFS within 3 months is set as the primary endpoint. The evaluation period is set at 3 months, because, in patients receiving eight courses (6 months) of capecitabine plus oxaliplatin as adjuvant chemotherapy after surgery of colorectal cancer, the incidence of HFS increased until the 4th course (at 3 months after the start of treatment) and then plateaued [37]. In addition, the median time of onset of grade ≥ 2 HFS induced by fluoropyrimidine anticancer drugs has been reported to be approximately 100 days [38, 39]. Therefore, evaluating the incidence of grade ≥ 2 HFS at 3 months is deemed appropriate as the primary endpoint. The majority of participants are expected to be patients with colorectal cancer, receiving capecitabine as adjuvant chemotherapy, which is typically recommended for at least 4 courses (3 months). In Japan, capecitabine plus oxaliplatin in combination with bevacizumab is the most commonly used palliative chemotherapy, with a reported median progression-free survival time of approximately 10 months [39]. The second major population will consist of patients with breast cancer. The median progression-free survival of capecitabine monotherapy in patients with advanced breast cancer has been reported as approximately 3.2 months [7]. Thus, it is expected that most participants will continue capecitabine for 3 months, facilitating the evaluation of the primary endpoint.

The expectation of a 15% reduction in the frequency of HFS is based on a study using celecoxib as the study drug, where the incidence of grade ≥ 2 HFS was reduced by approximately 20% compared with the placebo group [19, 20]. Based on these reports, we expect that a 15% reduction in incidence of HFS would provide a lower risk and equally effective preventive method compared to celecoxib.

The secondary endpoints include the time to onset of grade ≥ 2 HFS, the time to onset of grade ≥ 1 HFS within 3 months, incidences of dose reduction, schedule delay, discontinuation due to capecitabine-induced HFS, an incidence of grade ≥ 2 peripheral sensory neuropathy, and an incidence of any grade capecitabine-related adverse events (nausea, vomiting, appetite loss, diarrhea, oral mucositis, pigmentation, abnormality of liver and renal functions, and neutropenia). It is anticipated that preventing HFS with diclofenac cream may improve the dose intensity of capecitabine. However, there is a concern that capecitabine-related adverse events (nausea, vomiting, anorexia, diarrhea, mucositis, pigmentation, liver dysfunction, renal dysfunction, myelosuppression) may be exacerbated. Peripheral sensory neuropathy is also included as a secondary endpoint, assuming that absence of grade ≥ 2 HFS may alleviate some symptoms of neuropathy induced by oxaliplatin. This study will also include the following subgroup analyses: (i) frequency of grade ≥ 2 peripheral sensory neuropathy in patients treated with oxaliplatin, (ii) cumulative dose of capecitabine in the diclofenac and placebo groups, and (iii) frequency and severity of HFS, assessed separately for the palms and soles.

The stratification factors for randomization include the dose of capecitabine and sex, as the incidence of HFS depends on capecitabine dose. Additionally, capecitabine-related adverse events differ between sexes [40, 41]. Body composition also varies between women and men [42, 43]. A previous study showed that female patients with colorectal cancer experienced more dose-limiting toxicity than male patients when capecitabine was administered based on body surface area [41] (Fig. 1).

**Fig. 1 Fig1:**
[figure not shown]
Study scheme. Randomization will be conducted using a minimization method, adjusting for sex (male vs. female) and planned dose of capecitabine ([1] ≥ 800 mg/m^2^, < 1000 mg/m^2^, [2] ≥ 1000, < 1250 mg/m^2^, [3] ≥ 1250 mg/m^2^). Topical hydrocortisone butyrate 0.1%, diclofenac sodium 0.1% cream, or placebo cream will be applied to the palms and soles daily in the morning and evening for 3 months. To maintain self-adherence, all patients will receive standard self-care education at the start of chemotherapy, and the number of study agents used regularly by clinical pharmacists will be confirmed. Clinical pharmacists will regularly educate patients to improve their adherence to intervention protocols

If the J-DIRECT study demonstrates the prophylactic efficacy of diclofenac sodium 0.1% cream against capecitabine-induced HFS, it could establish a new preventive therapy for HFS. In addition, the suppression of HFS with topical diclofenac cream may improve the efficacy of high-dose intensity capecitabine-based chemotherapy.

## Data Availability

The data that support the findings of this study are available from the corresponding author, YI, upon reasonable request. Only clinical data managers at the central data center have access to reported case data through the EDC system during the study period. The data manager will transfer the final data set to the principal investigator and the data will be stored in the electronic format.

## Abbreviations

CAPEOX: Capecitabine plus intravenous oxaliplatin
FOLFOX: 5-Fluorouracil and leucovorin plus oxaliplatin
HFS: Hand-foot syndrome
jRCT: Japan Registry of Clinical Trials
QOL: Quality of life
RCT: Randomized-controlled trial
